#### H1

Alcohol withdrawal will increase working memory deficits, impulsivity and cognitive flexibility deficits in adult rats.

#### H2

Cognitive dysfunctions observed will be linked to changes in central biomarker of synaptic functions, changes in various neurotransmitter related activity and peripheral signs of neuroinflammation.

#### H3a

Pharmacological interventions targeting the GABAergic system will contribute to better working memory function, cognitive flexibility and reduced impulsivity during withdrawal.

#### H3b

Pharmacological interventions targeting the noradrenergic system will contribute to better cognitive functions and reduced alcohol seeking behaviors.

#### H3c

Pharmacological interventions targeting the inflammasome will reduce signs of neuroinflammation, indirectly contributing to better cognitive health.

This project will also generate a sample repository (brain, blood, plasma) for investigation and discovery of peripheral and central biomarkers indexing putative mechanisms involved in AUD and executive dysfunction, that could be used for follow-up biomarker analyses.

### Methods and planned analyses

Male and female Long Evans rats, 3 months old at study initiation, will be utilized in this study. Rats will be habituated to consume a liquid diet (Nestlé^®^ Chocolate Protein Boost) in which ethanol can be diluted. After baseline assessment of EFs, half of each cohort will be exposed to a diet supplemented with 10% w/v alcohol 5 days per week. Removal on 2 consecutive days per week will induce a withdrawal period. Such cycle will be repeated 4 times, with assessment of cognitive functions during withdrawal after 4 cycles (**Figure 4**; top panel, orange box).

**Figure 4 f4:**
[figure not shown]
Design of the experiment for cohort of 48 rats. Drugs proposed for this study will be Naltrexone, a5PAM or MC9950. Animals will be tested on different cognitive tasks, depending on their group affiliation (Inhibition/Working Memory or Set-shifting). Blood will be collected on a regular basis to control for the blood alcohol level, and brains will be collected at the end of the study for downstream analysis. Ctrl, control; EtOH, ethanol.

#### Measures

Three domains of EF (inhibition, working memory, set-shifting) will be assessed to match assessment in P1. Inhibition will be measured using the 5-Choice Serial Reaction Time Task (5-CSRTT). This test is conducted in operant conditioning boxes with 5 apertures featuring integrated light stimuli (193), and a reward dispenser on the opposite wall. Rats are trained to respond to a stimulus among the 5 apertures, earning a reward on a fixed intertrial interval. Lengthening this interval challenges rats to wait longer before responding, with premature responses during the intertrial interval serving as a reliable measure of response inhibition (or impulsivity). In alcohol-exposed rats, premature responses are expected to increase, especially when the intertrial interval is extended.

Working memory will be assessed using a T-maze spontaneous alternation task (194). After 2 days of habituation, rats explore the maze starting in the maze’s initial arm and then choosing between the two goal arms. The chosen arm is closed off, and the rat returns to the start arm for the next trial. This process is repeated for seven trials. Rats naturally alternate between arms, relying on working memory for novel environment exploration. Alcohol-exposed rats tested during withdrawal are expected to show diminished working memory functions.

Set-shifting will be evaluated following Floresco et al.’s protocol (195), in which rats undergo initial training in standard operant conditioning chambers with a house light, two retractable levers, and stimulus lights. Training involves a fixed ratio 1 schedule on each lever, reaching a criterion of 50 rewards or 30 minutes per lever. The second phase introduces a 90-trial session where rats must press a lever within 10 seconds to receive a reward. Visual cue discrimination training follows, with stimulus lights above the levers. Rats respond within 10 seconds to the lit lever for a sucrose reward, while responses on the non-lit lever are punished. Criterion: 10 consecutive correct responses for 30 trials over 4 days. After visual discrimination is learned, rats are tested in a “shift to response discrimination” task, where the rewarded lever is consistent, irrespective of the light stimulus. The number of trials needed to learn this new set serves as a proxy for set-shifting. Rules are modified after each testing session to ensure continual adaptation. Due to the complexity of the inhibition and set-shifting task, these cannot be run in the same animals. Therefore, different animals will be used to run inhibition and working memory vs set-shifting.

Following the assessment of alcohol-induced cognitive function changes, interventions will commence (Objective 2). Treatments involve intraperitoneal administration of drugs targeting α5-GABAA receptors (GL-II-73), the inflammasome (MCC950), the α2-noradrenergic receptor (guanfacine), and the opioid system (naltrexone). Initially, acute dosing will be explored using a Latin square design to test multiple doses (**Table 3**). Conducting multiple doses in the same animal necessitates several testing sessions, and all employed tests, such as the Y maze and 5-CSRTT, are stable and unaffected by practice and repetition (193, 196–198). The set-shifting task (195) can be adapted to establish new rules at each testing session, enabling regular assessment of set-shifting abilities in the same animals while mitigating the impact of practice on repeated testing.

**Table 3 T3:** Low, medium and high doses for each drug tested in Project 5.

Mg/kg	Low dose	Medium dose	High dose
Naltrexone	0.1	0.3	1
α5PAM	3	10	30
MCC950	1	3	10

Blood samples will be drawn weekly and 24 hours after discontinuation of the liquid diet (**Figure 4**) to verify 1) blood alcohol levels (BALs) exceeding 100mg% during exposure and 2) the absence of alcohol 24 hours after cessation when behavioral testing begins. BALs will be assessed using an ANALOX machine. Serum samples will also be utilized for measuring peripheral inflammasome biomarkers. Inflammasome activity will be determined by the phosphorylated/non-phosphorylated NALP3 ratio in peripheral blood mononuclear cells, along with investigating inflammatory markers (NF-KB, ERK, p38MAPK) and cytokines (IL-1β, IL-18, Caspase-1). Luminex xMAP technology^®^ will be employed for biomarker analyses.

After behavioral assessments, rats will be euthanized, and brains dissected for immunofluorescence staining and molecular analyses on regions of interest (prefrontal cortex, VTA, nucleus accumbens and hippocampus). Rostro-caudal coronal sections will be stored at -20°C for neuroinflammation, noradrenergic, and GABAergic marker analysis. RNA and proteins will be extracted from homogenized tissue, allowing for cDNA conversion, quantitative PCR, and Western Blot analyses. The markers examined include, but are not limited to, SST, PV, α5-GABRA, α1 GABRA, BDNF, and other GABAergic markers. Similarly, qPCR, immunostaining, and Western Blot analyses against sterile inflammation biomarkers (NALP3, NF-KB, ERK, p38MAPK, IL-1β, IL-18, Caspase-1) will validate the correlation of peripheral and central biomarkers in a region-specific manner. Investigation of changes in noradrenergic system markers (NET, α1 receptor, α2 receptor) will complement NM-MRI work outlined in P2.

The blood and brain samples collected will form a repository for subsequent biomarker analyses related to executive dysfunction in AUD. As Objective 3 establishes this repository, the analysis of these samples (peripheral or central) will be influenced by findings from other projects. Consequently, additional exploratory investigations of biomarkers will be conducted in these samples when other projects identify relevant pathways or markers in the clinical population.

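### Project 5 asserts that its working-memory test is unaffected by repetition, without support for the T-maze it describes, and its dose analysis has no session term

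*Protocol article*

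**What the plan says.** All references are to Project 5 of the protocol article.

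- **Working-memory test (Measures).** "Working memory will be assessed using a T-maze spontaneous alternation task". The rationale is that "Rats naturally alternate between arms, relying on working memory for novel environment exploration". Two days of habituation come first, and of the choice procedure the article says "This process is repeated for seven trials".
- **Dosing (Measures).** "Initially, acute dosing will be explored using a Latin square design to test multiple doses". The article accepts that "Conducting multiple doses in the same animal necessitates several testing sessions" and defends this by saying that "all employed tests, such as the Y maze and 5-CSRTT, are stable and unaffected by practice and repetition". The references given are 193 and 196–198. The T-maze's own reference, 194, is not among them.
- **Set-shifting (Measures, next sentence).** New rules can be set at each session, so that practice has less influence on repeated testing.
- **Sessions before dosing (Methods and planned analyses).** Executive function is assessed at baseline, and again in withdrawal after four alcohol cycles.
- **Doses (Table 3).** Three levels per listed drug. No vehicle session is stated.
- **Analysis (Proposed analyses).** Objective 2 uses separate two-way analyses of variance with diet and treatment as the factors, followed by Dunnett comparisons. Session is not named.

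**The concern.** The within-rat dose comparison needs each test to behave the same way at its later administrations as at its first. For the working-memory test, the article's only support is one sentence, and that sentence has two weaknesses. It names a maze that the methods do not describe and leaves out the one they do. It also claims stability for every test used, while the next sentence treats set-shifting as needing protection against practice.

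The question matters most for the T-maze, because the article itself links alternation to novelty. If alternation drifted toward the 50% chance level over sessions, two things could follow. The drift could add noise to the dose comparison, or it could leave less room for a drug to show an effect. Either would weaken the working-memory part of H3a. A model with only diet and treatment could not separate a session trend from residual error.

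**Working it through.** The article gives no power, variance or decline figure for this comparison, so there is no stated figure to reproduce. The text was compared directly, and the possible consequences were then sized under labelled assumptions.

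**1. Consistency.** The T-maze is described and the Y maze is cited for stability. The Y maze occurs nowhere else. The word "all" in the claim formally covers the T-maze, but no T-maze evidence is named.

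**2. Number of scored sessions on one drug**, assuming the maze is run at each assessment and once per dose: 1 baseline + 1 withdrawal + 3 doses = 5, or 6 if a vehicle session is added.

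**3. Precision of one rat's session score.** Assume 75% alternation and at most seven scored choices. The variance is 0.75 × 0.25 / 7 = 0.0268, so the standard error is √0.0268 = 0.164, or about 16 points.

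**4. Additive drift.** Take a cyclic 4 × 4 Latin square (vehicle and three doses), with assumed true dose contrasts of 0.05, 0.10 and 0.15 and session effects of 0, −0.05, −0.10 and −0.15. The dose means return contrasts of 0.05, 0.10 and 0.15 exactly, so there is no bias.

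Without a session term, the drift goes into residual error. The session effects in points deviate from their mean by 7.5, 2.5, −2.5 and −7.5. Their variance is (56.25 + 6.25 + 6.25 + 56.25) / 4 = 31.25. Against the binomial variance of 267.9 points² from step 3, this is 31.25 / 267.9 = 11.7% extra. The share is smaller if rats also differ from one another.

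**5. Fading drug effect.** Let a fraction r of the drug effect survive each further session. Over k dose sessions, the mean retained effect is m = (1 + r + … + r^(k−1)) / k, and the required sample size grows by 1/m².

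| r (assumed) | k = 3: m | k = 3: 1/m² | k = 4: m | k = 4: 1/m² |
|---|---|---|---|---|
| 1.0 | 100% | 1.00 | 100% | 1.00 |
| 0.9 | 90% | 1.23 | 86% | 1.35 |
| 0.8 | 81% | 1.51 | 74% | 1.84 |
| 0.5 | 58% | 2.94 | 47% | 4.55 |

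In the 4 × 4 square with r = 0.8, true contrasts of 0.05, 0.10 and 0.15 appear as 0.037, 0.074 and 0.111. Balancing the order does not remove this attenuation. Nothing in the article says where r lies, and r = 1 (no loss) is possible.

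**The case against.** The strongest reply has four parts.

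- **The maze name may be a slip.** The sentence offers the Y maze only as an example and cites sources that cannot be checked here. They may support repeated alternation testing. This stands, and it is why the request is to support or narrow the claim, not to declare it false.
- **Novelty may be within-session.** The plan deliberately habituates the rats: "After 2 days of habituation, rats explore the maze starting in the maze’s initial arm". The apparatus is then already familiar at the first scored trial. The relevant novelty may be the arm less recently visited, which need not fade across sessions. This is a fair reading, and it means a decline cannot be presumed.
- **The Latin square balances order.** A reader might infer that rats tested later look impaired whatever the dose, and that this distorts the dose comparison. Step 4 shows that it does not: an additive trend cancels from balanced dose contrasts. What remains is lost precision, or attenuation if the drug effect itself shrinks.
- **A condensed article may omit model terms.** A fuller plan may include session. However, the article does name the factors of the Objective 2 analysis, and a statement that repetition has no effect gives an analyst no reason to add one.

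The set-shifting comparison should also not be pressed too far. That task scores the learning of a new rule, so the rule has to change for the test to be repeated. It shows only that the blanket wording about all tests is too broad.

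**Conclusion.** The point holds in a limited form. The article is inconsistent about which maze is used. Its stability statement is broader than its own next sentence allows. Repeat-test stability of T-maze alternation over at least five scored sessions is asserted without named support.

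A reader might go further and conclude that later dose sessions lose the working-memory signal, or that an effective drug would be missed. The document does not support that. It reports no decline, and the habituation step allows a benign reading. The figures above rest entirely on assumed drift or retention rates and run from no loss to a large one.

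The demonstrable gap is small. The stated model has no place for a session trend, although the design supplies that factor. This is a low-cost improvement to a preclinical component, not a flaw that invalidates it.

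**What to change.** 1. In Measures, reconcile the two maze names. Limit the stability statement to the tests for which support is given, and cite that support for the maze actually used.
2. In Proposed analyses, add session (period) as a factor to the diet-by-treatment analysis of the Latin-square dose data. This costs two degrees of freedom with three dose sessions, or three with four. It removes an additive trend from residual error but does not restore a compressed drug effect.
3. Report control-diet rats' alternation at each session, with dose accounted for, as a check that the measure keeps its range above 50%. A clear fall would warn that a null working-memory result may reflect the test and not the drug.

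None of this needs extra animals, sessions or equipment. Changing the maze context at each session, or falling back on first dose sessions only, is not asked for. The first would work against the habituation step, and the second would give up the within-rat comparison.

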#### Proposed analyses

Behavioral data will be examined to assess the impact of alcohol exposure on EFs, utilizing ANOVA (or relevant non-parametric alternatives) followed by Tukey’s *post hoc* comparisons for statistical significance. In the alcohol-exposed groups, it is possible to observe subgroups of animals with higher susceptibility to alcohol than the others, suggesting existence of high-responders and low-responders.

For data collected weekly, data will be analyzed with repeated measures to identify animals that are more than 50% of the time over the mean, and animals that are more than 50% of the time under the mean to segregate high-responders and low-responders respectively. If such separation does not exist consistently, then analyses will focus on overall alcohol effect. For the second objective involving drug interactions, separate 2-way ANOVA with diet and treatment as factors will be applied, followed by Dunnett’s *post-hoc* comparisons (198). In Objective #3, blood sample data will be analyzed using Student’s t-test (Objective #1) or 2-way ANOVA (Objective #2) with diet and treatment as factors, followed by Dunnett’s *post-hoc* test. Brain analyses with qPCR and Western Blot will use 2-way ANOVA with diet and treatment as factors, followed by Dunnett’s *post-hoc* comparisons. Pearson or Spearman analyses will evaluate correlations between executive dysfunction and peripheral/central biomarker levels, with p-values adjusted for multiple comparisons using the Bonferroni method due to the potential high number of pairwise analyses.

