This investigation will target specific biological pathways implicated in EF deficits in AUD, and investigated correlationally across the rest of CDiA. Specifically, P5 will focus on GABAergic neurotransmission, the inflammasome system, the noradrenergic system, and the opioid system. The GABAergic system plays a critical role in cognitive functions (184), and will be investigated as a therapeutic mediator of neuromodulation treatment in P4. To complement findings from P4, P5 will enhance GABA activity pharmacologically during withdrawal in rats to investigate its impact on EFs. Similarly, the activity of the inflammasome, implicated in brain disorders (185) and alcohol consumption (186), will be measured in P3 for its translational biomarker value. To complement and extend P3’s correlational findings, P5 will block inflammasome activity pharmacologically (via MCC950), to assess its impact on EFs. The integrity of the noradrenergic system, to be measured through NM-MRI in P2, plays a critical modulatory role in AUDs (187), with complex effects depending on activity at various receptor subtypes (α1 versus α2). P5 will target the α2-noradrenergic receptor, using guanfacine, an α2-receptor agonist that demonstrated efficacy at reducing alcohol consumption in rats (188) and is used for the treatment of attention-deficit/hyperactivity disorder (189).

Finally, naltrexone is a prescribed medication used to manage alcohol dependence, especially consumption, although it appears to have reduced efficacy in certain patients, depending on gender and genetic differences (190). Naltrexone is predicted to be prescribed in a significant proportion of P1 participants. Its effects on EFs are not fully characterized and tend to vary from study to study (191, 192). Here, we propose to systematically investigate the relationship between its known clinical efficacy on consumption and potential improvement of EFs in rats, providing a clinically-relevant comparison to the other interventions.

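### Project 5 uses both sexes of rat, but its stated two-factor ANOVAs and t-test leave sex in the error term, which costs power in between-animal comparisons

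*Protocol article*

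**What the plan says.** All references are to Project 5 of the protocol article.

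- **Animals** (Methods and planned analyses): "Male and female Long Evans rats, 3 months old at study initiation, will be utilized in this study".
- **Diet allocation** (same section): "half of each cohort will be exposed to a diet supplemented with 10% w/v alcohol 5 days per week".
- **Cohort size** (Figure 4 caption): "Design of the experiment for cohort of 48 rats". The number of cohorts is not given.
- **Task groups** (Measures): "different animals will be used to run inhibition and working memory vs set-shifting".
- **Objective 2 behaviour** (Proposed analyses): "separate 2-way ANOVA with diet and treatment as factors will be applied", followed by Dunnett comparisons.
- **Blood** (same section): a Student t-test for Objective 1, and "2-way ANOVA (Objective #2) with diet and treatment as factors".
- **Brain qPCR and Western blot** (same section): again a two-way ANOVA on diet and treatment.
- **Objective 1 behaviour** (same section): ANOVA or a non-parametric alternative, with no factors named.

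Sex does not appear in these analyses as a factor, block, covariate or stratum. The Background says of naltrexone, one of the study drugs, that "it appears to have reduced efficacy in certain patients, depending on gender and genetic differences".

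**The concern.** Sex is known for every animal before any outcome is measured. If males and females differ in task performance, alcohol intake or marker level, a model with diet and treatment alone counts that difference as noise. The diet contrast and the other between-animal contrasts are then judged against a larger error variance than the design requires, in groups that are already small because the two task sets use separate animals.

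A second consequence is that a two-factor model has no term that could show a drug acting differently in the two sexes. A response confined to one sex would be averaged with the absence of response in the other.

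This goes beyond a detail left to a fuller plan. The article names the ANOVA factors three times, and each time the list omits a variable that the design brings in.

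**Working it through.** Project 5 states no power, effect size, SD or alpha, so there is no figure of its own to reproduce. What follows is an illustration.

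**Inputs from the document.** One cohort is 48 rats, half of them on alcohol; both sexes are used; the two task sets use different animals.

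**Assumptions.** The task split is equal and the sexes are balanced within cells, so 48/2 = 24 rats per task set, 24/2 = 12 per diet and 12/2 = 6 per sex per diet. Two-sided alpha is 0.05. The diet effect is d = 1.2 within-cell SD, chosen to give 80% power with sex in the model. The sex difference s, in within-cell SD, is varied.

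**Step 1: error variance.** Leaving out a balanced sex difference of s multiplies the error variance by about 1 + s²/4.

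**Step 2: power.** For n rats per diet, the noncentrality of the diet F test is n·d²/2 divided by that multiplier. With sex in the model it is 12 × 1.44 / 2 = 8.64, which on 1 and 21 df gives 80.0% power. Without sex the error df are 22:

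| s | multiplier | noncentrality | power without sex |
|---|---|---|---|
| 0 | 1.00 | 8.64 | 80.2% |
| 0.5 | 1.0625 | 8.13 | 77.8% |
| 0.8 | 1.16 | 7.45 | 74.2% |
| 1.2 | 1.36 | 6.35 | 67.3% |
| 1.6 | 1.64 | 5.27 | 59.3% |

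**Step 3: does a treatment factor change this?** The table has diet alone. In a 2×2 diet-by-treatment layout with the same 24 rats, the error df are 20 without sex and 19 with it, and d = 1.206 gives 80% power with sex included. Power for diet without sex is then 77.8%, 74.2% and 67.4% at s = 0.5, 0.8 and 1.2. The loss is the same. With 48 rats in one analysis (24 per diet, d = 0.827) it is 77.6% and 74.0% at s = 0.5 and 0.8.

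**Step 4: type I error.** Simulating the diet-only model with 12 rats per diet and no diet effect, the rejection rate at a nominal 5% is about 4.2%, 3.5% and 2.2% at s = 0.5, 0.8 and 1.2. With sex in the model it stays at 5%. The two-factor test errs on the cautious side.

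**Step 5: what an interaction term could show.** Take an effect of 1.2 SD in one sex and none in the other, with 6 rats in each of four cells. The interaction contrast has standard error √(4/6) = 0.816, so its noncentrality is 1.2/0.816 = 1.47. On 20 df the power is about 29%.

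**The case against.** The strongest reply is that this is a one-paragraph summary for a preclinical project in a seven-project article. It states no power target that could be missed, and it does not say that only these factors will be used. The sex differences that produce the larger losses are assumed and have no source in the document; at 0.5 SD the loss is about two points. These points stand, and they limit the claim to a modest one. They do not remove it, because the factors are named and a better model is available at almost no cost.

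Four stronger readings are tempting, and the document does not support them.

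- **That cohort variation also inflates the error.** The wording about half of each cohort suggests more than one cohort, but no pooling is stated. The Figure 4 caption joins the drugs with an or, and the Objective 2 ANOVAs are called separate. One drug and one ANOVA per cohort is a natural reading, and cohort then adds nothing to the error.
- **That every drug effect loses power.** Measures describes doses tested in the same animal by Latin square. If these are analysed within animal, the sex main effect cancels from the dose contrasts. Proposed analyses does not state repeated measures for Objective 2, so this is open.
- **That the document predicts a sex effect in rats.** The naltrexone remark is hedged and concerns patients, and no Project 5 hypothesis is about sex.
- **That Objective 1 behaviour excludes sex.** That ANOVA names no factors, so a sex term is not ruled out there.

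**Conclusion.** The point holds in a limited form. Where both sexes enter a between-animal comparison and the stated model has diet and treatment alone, or is a t-test, any sex difference goes into the residual. A reader might infer that the tests are invalid or produce too many false positives. With the sexes balanced the opposite is true: they are conservative and less powerful.

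Under the stated assumptions the cost is about 2, 6 or 13 percentage points of power for sex differences of 0.5, 0.8 or 1.2 SD, and nil if there is no difference. Those differences, the equal task split and the balance of the sexes are assumptions; the document gives none of them. The point concerns the preclinical project only and does not touch the randomised trial in Project 4.

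**What to change.** In Project 5, Proposed analyses:

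1. Add sex as a blocking factor to the diet-by-treatment ANOVAs for behaviour, blood and brain, and name it in the Objective 1 behaviour ANOVA.
2. Replace the Objective 1 blood t-test with a model on diet and sex.
3. State that sex is balanced within each diet-by-task cell.
4. Add cohort as a block only where a single analysis pools cohorts.
5. Report sex-by-treatment as exploratory and say that its power is low.

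The cost is a change of wording and no extra animals. Sex takes one error degree of freedom, cohort one for each pooled cohort beyond the first, and the interaction one fewer than the number of treatment levels. If the sexes turn out not to differ, adding sex changes power in the illustration from 80.2% to 80.0%.
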